1.2.2 CRITERIA FOR WITHDRAWAL

*1.2.2.1 Criteria for mandatory discontinuation of treatment*

- Consent withdrawal by the patient
- High suicide risk according to investigator’s judgment or any suicide attempts during the study whatever its severity
- Worsening of PTSD symptoms, which in the opinion of the investigator requires an adaptation of treatment not compatible with the protocol or requires hospitalization.

*1.2.2.2 Other possible reasons for premature discontinuation of treatment*

- Any adverse event or circumstances justifying the discontinuation of the treatment in the investigator’s opinion.
- Treatment failure
- Protocol deviation which jeopardizes the patient’s safety

We will record the reason and the exact time of the premature discontinuation of treatment in the case report form (CRF). If more than one reason is given, we will indicate the main reason according to good clinical practice (GCP).

1.2.3 SIDE EFFECTS PROCEDURES

An Adverse Event (AE) in this trial is any untoward medical occurrence regardless of its causal relationship with TF-CBT. AE is assessed at each clinician visit using the SMURF and is classified by the investigator as mild, moderate or severe:

- **Mild:** Acceptable. The subject is awareness of symptoms or signs, but they are easy tolerated.
- **Moderate:** Disturbing. The AE is discomfort enough to interfere with usual daily activity.
- **Severe:** Unacceptable. The subject is unable to work or to do usual daily activities (e.g. death, life-threatening, significant incapacity).

If the AE is regarded as severe, it will be defined as a Serious Adverse Event (SAE). SAEs will be reported in detail to Socialstyrelsen (responsible for side effects in psychological treatments) and will also be stored in the CRF.

Additionally, each AE is to be classified with Assessment of Causality (stored in the CRF):

- **Unlikely:** The event is most likely related to an aetiology other than TF-CBT.
- **Possible:** A causal relationship is conceivable and cannot be dismissed.
- **Probably:** Good reason and sufficient documentation to assume a causal relationship.

If an SAE is at least possibly related to TF-CBT treatment, then it is also to be classified by the investigator as expected or unexpected. An unexpected SAE is defined as a Suspected Unexpected Serious Adverse Reaction (SUSAR). It is expected if it is already known from earlier CBT trials or is mentioned in relevant documents. This will also be directly reported to Socialstyrelsen with follow-up information describing the outcome of the SAE and action taken will be reported as soon as it is available.

In addition, three interim analyses will be conducted by KTA to ensure that the TF-CBT group is not associated with any significant worsening of symptoms. Thus, we have taken extensive steps in order to monitor and record any possible side effects associated with TF-CBT.

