Participants randomized to TF-CBT will receive a brief 3-session intervention provided within 72 hours after the accident. In this treatment, the patient is instructed to systematically expose him/herself to the fearful memory of the event and stay in this memory until the anxiety has attenuated. By doing this exposure repeated times, the association between the memory and fear response is hypothesized to be gradually extinguished. The placebo group will receive sham treatment i.e. written information about PTSD and how to treat it but without any therapist-guided interventions.

We will measure PTSD symptoms using the Clinician Administered PTSD Scale (CAPS; the gold standard for PTSD assessment) and Posttraumatic Diagnostic Scale,[^22^](#_ENREF_22)^,^[^23^](#_ENREF_23) depression using the Montgomery Åsberg Depression Rating Scale – Self rated (MADRS-S),[^24^](#_ENREF_24) quality of life using the EQ-5D[^25^](#_ENREF_25) and treatment side effects using the Safety Monitoring Uniform Report Form (SMURF)[^26^](#_ENREF_26) at baseline (i.e. before treatment allocation), 2-, 6-, 12-, 24-, 48- and 120 months using blinded assessors. Primary endpoint is set to 6-months after the trauma. Patients unable to come to the clinic for follow-up assessments will be interviewed via telephone or skype.

The primary outcome (significant PTSD symptoms assessed by the CAPS) will be analyzed using risk ratios and numbers-needed-to-treat with 95% confidence intervals. Continuous data will be analyzed in a mixed-effects model adjusting for data attrition (covariance and residual structure will be set based on the best model fit of the data) using intention-to-treat design. Effect sizes for continuous measures will be estimated using Cohen´s *d*. Assessor´s blindness will be also tested (each assessor will guess treatment allocation for each participant and this will be tested in a logistic regression with guess as independent variable and allocation as dependent variable). A flowchart of the treatment study is shown in the attached figure.

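### SAE status depends on the severity grade alone, so a suicide attempt graded mild or moderate is not an SAE; the sections on when AEs are collected also disagree

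*Protocol*

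**What the plan says.** **Seriousness.** Protocol Methods 1.2.3 grades every adverse event as mild, moderate or severe. Moderate means: "The AE is discomfort enough to interfere with usual daily activity". Severe means: "The subject is unable to work or to do usual daily activities (e.g. death, life-threatening, significant incapacity". Serious status is then taken from the grade: "If the AE is regarded as severe, it will be defined as a Serious Adverse Event (SAE". The consequence is external reporting: "SAEs will be reported in detail to Socialstyrelsen". The SUSAR step starts from an SAE that is at least possibly related to TF-CBT and is unexpected. No other criterion for seriousness is given.

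**Events singled out elsewhere.** Methods 1.2.2 lists mandatory reasons for discontinuing treatment. They include "any suicide attempts during the study whatever its severity" and PTSD worsening that, in the investigator's opinion, "requires an adaptation of treatment not compatible with the protocol or requires hospitalization".

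**Collection.** Methods 1.1 places the SMURF at baseline, before allocation, and at months 2, 6, 12, 24, 48 and 120, with blinded assessors and no distinction between arms. Methods 1.2.3 says: "AE is assessed at each clinician visit using the SMURF". It does not say what a clinician visit is. Between randomisation and month 2 the TF-CBT arm has three therapist sessions; the control arm receives written material "without any therapist-guided interventions".

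**The concern.** Severity describes how intense an event is. Seriousness describes what it led to or threatened. When one is derived from the other, the serious category can take in events that do not belong there and leave out events that do. The second error matters more here. The trial has a specific worry about harm: Introduction 2.2.1 criticises the earlier trial for lacking systematic side-effect data and recalls that debriefing made symptoms worse. A suicide attempt is the kind of event such monitoring exists to catch.

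The collection question affects whether adverse-event counts can be compared between arms. If one arm is asked more often, and by someone who knows the allocation, it can show more events with no difference in harm.

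**Working it through.** **Part 1: the SAE rule, applied as written.** This part is textual and the protocol gives no figure to reproduce. The sample size of 352 plays no role in it.

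| Event | Grade given | SAE under 1.2.3? | Can reach the SUSAR step? | Singled out in 1.2.2? |
|---|---|---|---|---|
| Any AE that stops the patient working | severe, by definition | yes, reportable | yes, if possibly related and unexpected | not as such |
| Suicide attempt | severe | yes | yes, on the same condition | yes |
| Suicide attempt | mild or moderate | no | no | yes, at any severity |
| PTSD worsening that leads to hospital care | severe | yes | yes, on the same condition | yes |
| PTSD worsening that leads to hospital care | mild or moderate | no | no | yes |

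- The first row is the over-inclusive side. Patients come from a trauma centre, and an AE counts whatever its cause. A later complication of the injury that keeps someone off work therefore qualifies.
- The third and fifth rows are the under-inclusive side. The wording of 1.2.2 shows that the authors foresee suicide attempts of low severity. Nothing in 1.2.3 obliges the investigator to grade such an attempt severe, and hospitalisation is not named there at all.

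**Part 2: number of enquiries after randomisation, up to and including month 2.**

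Inputs from Methods 1.1: three sessions in TF-CBT, no therapist contact described for controls, and one SMURF assessment at month 2 in both arms.

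- If sessions count as clinician visits: 3 + 1 = 4 in TF-CBT and 0 + 1 = 1 in control.
- Under the Methods 1.1 schedule: 1 and 1.

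The effect in the first case needs an assumption that the protocol does not supply. Let the true AE risk be equal in both arms, let each event be detectable at every contact, and let each contact capture it independently with probability q. The true risk cancels, and the ratio of recorded risks is

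RR = [1 − (1 − q)^4] / q

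| q (assumed) | Numerator | RR |
|---|---|---|
| 0.3 | 1 − 0.7^4 = 0.7599 | 2.53 |
| 0.5 | 1 − 0.5^4 = 0.9375 | 1.88 |
| 0.7 | 1 − 0.3^4 = 0.9919 | 1.42 |
| 0.9 | 1 − 0.1^4 = 0.9999 | 1.11 |
| 1.0 | 1 | 1.00 |

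Under the Methods 1.1 schedule numerator and denominator are equal, so RR = 1.00 for every q.

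The table illustrates the direction and does not estimate the trial. Methods 1.1 places the intervention within 72 hours of the accident. An event that begins after the last session cannot be caught at a session, and a month-2 enquiry that looks back would recover many early events in controls. Both push the ratio towards 1.

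**The case against.** **On the SAE rule.** A patient in hospital would ordinarily be unable to carry on usual activities and so would be graded severe; a hospitalisation graded mild or moderate is an uncommon case. That largely stands. The low-severity suicide attempt is the stronger example. It can be said that such an attempt leads to discontinuation under 1.2.2, with reason and time recorded in the CRF. That stands in part. The event is not lost from the trial's records, but SAE status, the report to the authority and access to the SUSAR step are. The discontinuation record also helps only while there is treatment left to stop, and treatment is three sessions against follow-up to 120 months.

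Over-inclusion errs towards more reporting, and incapacity from the injury should be balanced by randomisation. Both are fair. A reader might infer that injury sequelae will dominate the SAE count, but the protocol gives no rate from which to say so.

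**On collection.** The phrase in 1.2.3 names the same instrument as Methods 1.1 and may be shorthand for the same scheduled visits. Collection is then equal and blinded. This stands, and it makes the bias conditional. Against it, under that reading no SMURF enquiry is scheduled between baseline and month 2, although 1.2.2 allows an adverse event to end treatment. The protocol does not settle which reading is meant. It also specifies no between-arm AE test, and it describes the interim analyses as looking for symptom worsening, not AE counts.

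**Conclusion.** The SAE rule is defective as written, and this needs no numerical assumption. It makes every work-stopping AE an SAE. It leaves outside SAE and SUSAR reporting any suicide attempt, or event involving hospitalisation, that is graded mild or moderate, and so does not match the events named in Methods 1.2.2. How many events this affects cannot be calculated from the protocol.

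The collection point is secondary. Methods 1.1 and 1.2.3 differ on when and by whom AEs are collected. If therapy sessions count, TF-CBT has three extra unblinded enquiries between randomisation and month 2, and an AE comparison would be biased against it by an amount that depends on assumed capture (RR 1.11 to 2.53 for q from 0.9 to 0.3). Under the Methods 1.1 schedule there is no bias.

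Two stronger readings are not supported. One is that AEs will in fact be miscounted against TF-CBT: this assumes that sessions count, and overlooks that both arms have a baseline SMURF and the same later schedule. The other is that control-arm safety data are compromised because causality is defined against TF-CBT: AEs are recorded whatever their cause, and no consequence of that definition can be shown.

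Safety is not one of the three numbered research questions. The primary outcome, sample size and error rates are unaffected. The point is worth acting on because the rule is explicit and cheap to correct.

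**What to change.** 1. In Methods 1.2.3, define seriousness by the outcome of the event and keep mild, moderate and severe as a separate intensity field. Reconcile the definition with the events named in 1.2.2, so that it is clear whether each is an SAE whatever its grade. This concerns classification and reporting only; it does not touch the discontinuation criteria.
2. Reconcile Methods 1.1 and 1.2.3: state what a clinician visit is, and when and by whom AEs are collected in each arm.
3. Base any between-arm AE comparison on the common blinded assessments, and list session-reported AEs separately for TF-CBT.

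The cost is a short protocol amendment and one added CRF field. The drawback is that session AEs leave the comparative table, though they are still listed. No change in sample size is needed.

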**2 IS TF-CBT A COST-EFFECTIVE TREATMENT IN PREVENTING THE DEVELOPMENT OF PTSD SYMPTOMS?**

2.1 OVERALL DESIGN

Patients from the randomized trial (research question 1) will be followed in the patient register (Patientregistret), the prescription register (Läkemedelsregistret) and the longitudinal integrated data-base for health insurance and work-related research (LISA - Longitudinell integrationsdatabas för sjukförsäkrings-och arbetsmarknadsstudier) Costs will be analyzed using a societal perspective i.e. including both sick leave, hospitalizations, medical use etc. and analyzed in relation to outcome (i.e. PTSD symptoms and also quality-adjusted life years which are assessed in the randomized trial using the CAPS and EQ-5D).

2.2 COST ESTIMATIONS

We will use national tariffs to estimate costs form different forms of health care visits as we have done previously in other cost-effectiveness studies (see publication list for more details). Productivity losses will be estimated using gross earning data from each patient. The treatment costs (i.e. the cost of having a full time psychologist at the emergency department) will be included in the cost estimation.

2.3 COST-EFFECTIVENESS ANALYSES

Cost-effectiveness comparisons will be analyzed using incremental cost-effectiveness ratios as well as the net benefit approach with different willingness-to-pay scenarios. Cost-effectiveness ratios are calculated as following: (Δ^C1^ – Δ^C2^)/(Δ^E1^ – Δ^E2^), where Δ^C1^ – Δ^C2^ is the difference in cost change (from pre- to follow-up) between the two treatment groups. Δ^E1^ – Δ^E2^ refers to the corresponding difference in clinical outcome (i.e. PTSD vs. no PTSD). Because cost-effectiveness is a relative term i.e. an intervention is only cost-effective depending on how much the society is willing to pay for one unit of improvement, we will also use the ”net benefit approach”, which estimates the cost-effectiveness depending on different societal willingness-to-pay values for one unit of improvement. The net benefit of each individual in this trial will be calculated according to the following formula: (λ x E) – Δ^C^ where λ is the willingness to pay (i.e. the different values that the society is willing to pay for one unit of improvement), E is the efficacy (i.e. PTSD status or gain on the EQ-5D), and Δ^C^ is the cost change from baseline to primary endpoint (6-months). We will calculate individual net benefits by assuming different values for λ and a regression model with non-parametric bootstrapping (one thousand replications) to estimate be difference between TF-CBT treatment-as-usual. Cost-effectiveness acceptability curves will be used to get a visual estimate of the total net benefit of TF-CBT.

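### Section 2.1 promises a QALY analysis, but the formulas in section 2.3 use an EQ-5D gain without a time dimension and leave the unit of willingness to pay open

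*Protocol*

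**What the plan says.** Protocol Methods 2.1 names two outcomes against which costs will be analysed: "PTSD symptoms and also quality-adjusted life years which are assessed in the randomized trial using the CAPS and EQ-5D".

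Methods 2.3 then fixes the formulas:

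- **ICER.** The denominator "refers to the corresponding difference in clinical outcome (i.e. PTSD vs. no PTSD"). No second, QALY-based ratio is given.
- **Net benefit.** This is computed per person as (λ × E) – ΔC. The benefit term reads "E is the efficacy (i.e. PTSD status or gain on the EQ-5D").
- **λ.** It stands for "the different values that the society is willing to pay for one unit of improvement". The unit is not named.
- **ΔC.** It "is the cost change from baseline to primary endpoint (6-months").

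Methods 1.1 schedules the EQ-5D "at baseline (i.e. before treatment allocation), 2-, 6-, 12-, 24-, 48- and 120 months using blinded assessors", so three measurements (0, 2 and 6 months) fall within the 6-month window.

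**The concern.** A QALY is utility multiplied by time. A gain between two visits is a difference in utility only. Section 2.1 therefore states a target that no formula in 2.3 reaches: the ICER counts PTSD cases, and the net benefit uses either PTSD status or an EQ-5D difference.

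What is at stake is how the EQ-5D net benefit and its acceptability curve can be read. If λ is per EQ-5D point, the curve is coherent but has no link to a per-QALY threshold. If λ is taken as per QALY, a gain seen at the end of half a year is credited as though it had been held for a full year. With positive incremental cost, the λ at which net benefit crosses zero is ΔC/E (arm differences), so it would look too low by the same factor by which E is too large.

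**Working it through.** The protocol states no EQ-5D, QALY or net-benefit figure, so there is nothing to reproduce. The check is how far an EQ-5D gain departs from the QALYs it would stand in for.

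**Inputs from the protocol**
- EQ-5D visits at 0, 2 and 6 months (Methods 1.1).
- Window of 6 months = 0.5 year (Methods 2.3). It is written for cost and is only implied for E.

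**Assumptions**
- No arm difference at baseline, as expected under randomisation.
- Linear interpolation between visits.
- Arm difference g at 6 months and f × g at 2 months. The protocol has no data on g or f.
- λ is per QALY. The protocol does not say this, so the result is conditional on it.

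**Area under the curve, in years**

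QALY difference = ½ × (2/12) × (0 + f)g + ½ × (4/12) × (f + 1)g
= g × [f/12 + (2f + 2)/12]
= g(3f + 2)/12

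Overstatement = g ÷ [g(3f + 2)/12] = 12/(3f + 2)

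| f (2-month difference ÷ 6-month difference) | QALYs per 1.0 of g | Overstatement | QALYs if g = 0.05 (illustrative) |
|---|---|---|---|
| 0 (appears only by month 6) | 0.167 | 6.0 | 0.0083 |
| 1/3 (linear growth) | 0.250 | 4.0 | 0.0125 |
| 1 (fully present at month 2) | 0.417 | 2.4 | 0.0208 |
| 1.5 | 0.542 | 1.85 | 0.0271 |
| 2 (early difference, then narrowing) | 0.667 | 1.5 | 0.0333 |

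**Break-even.** The ratio equals 1 when 3f + 2 = 12, so f = 10/3. For a positive 6-month difference, the two-point gain overstates QALYs unless the 2-month difference exceeds about 3.3 times the 6-month one. A difference in the wrong direction at 2 months pushes the ratio above 6: at f = –0.25 it is 12/1.25 = 9.6.

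**Analyses on PTSD status.** These do not use the EQ-5D. The ICER in 2.3 and the first-named version of E are untouched by any of this.

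**The case against.** The strongest defence is that this is loose wording. Section 2.1 ties QALYs to the EQ-5D, so an EQ-5D gain in 2.3 may be shorthand for QALYs gained, and the conversion (value set, interpolation, baseline adjustment) commonly belongs in the SAP, which is not at hand. The 6-month window is attached to cost, not explicitly to E. And if λ is per unit of whatever E measures, the formula is internally consistent.

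Part of this stands: the protocol does not commit to a per-QALY λ, so no overstatement is proven. But 2.3 does more than leave detail open. It writes the equation and defines each term, and the surrounding terms are two-point changes. If shorthand was meant, the same correction is needed. If λ is per EQ-5D point, the QALY analysis in 2.1 is still missing.

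A reader might also infer four stronger points, which the protocol does not support:

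- **That 2.4 to 6 is a firm range.** It holds only for f between 0 and 1. Methods-independent text in the Introduction (2.2.1) expects sizeable spontaneous recovery, so an early difference that later narrows (f above 1) is plausible.
- **That research question 2 gets a wrong answer.** That question concerns preventing PTSD symptoms, and the analyses on PTSD status are unaffected.
- **That an emergency-department baseline biases the EQ-5D gain through physical recovery.** Baseline precedes randomisation, so recovery from injury is balanced in expectation. It adds noise, not bias.
- **That using cost change is an error.** Under randomisation, cost change and accrued cost have the same expected arm difference, so only precision is at issue. With equal variances σ², the change score has variance 2(1 – ρ)σ² against (1 – ρ²)σ² after covariate adjustment, a ratio of 2/(1 + ρ): 1.54 at an assumed ρ of 0.3 and 1.18 at 0.7. The gap vanishes if baseline cost is a covariate, and 2.3 does not rule that out.

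**Conclusion.** The inconsistency between 2.1 and 2.3 is real and should be corrected. Followed as written, no formula in 2.3 yields a QALY, and the EQ-5D net benefit and acceptability curve cannot be read against a per-QALY threshold. This rests on the text alone.

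The size is conditional. If a per-QALY λ were applied to a two-point EQ-5D gain over 6 months, benefit would be overstated by 12/(3f + 2), with 4-fold for linear growth as a central illustration and 1.5- to 6-fold for f from 2 down to 0. This assumes baseline balance, linear interpolation, and a value of f on which the protocol is silent. The factor scales the EQ-5D effect whatever its sign, so an unfavourable effect would be magnified too. The conclusion is limited to the EQ-5D version.

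**What to change.** In Methods 2.3:

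1. For the EQ-5D version, define E as QALYs over 0–6 months by area under the EQ-5D utility curve at baseline, 2 and 6 months, with baseline utility as a covariate in the net-benefit regression.
2. State that λ is per QALY for this version and per PTSD case avoided for the PTSD version.
3. Add a QALY-based ICER beside the one on PTSD status, and build each acceptability curve on its own E and λ.
4. Optionally, for precision, use cost accrued to 6 months with baseline cost as a covariate in place of an unadjusted change score.

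The cost is a few sentences and a little more analysis. The 2-month EQ-5D and the register follow-up for costs are already planned, so nothing new is collected. The cost-effectiveness result may look less favourable than one based on EQ-5D points.

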# Scientific implications

This project holds important scientific implications:

First, there is to date only one early stage randomized controlled trial in the USA showing that PTSD can be prevented through TF-CBT. This current study is unique in providing an adequately powered test of the hypothesis using a larger sample size, allowing longer-term follow-up assessments, as well as appropriate monitoring of treatment side effects. In addition, the health economical analyses will reveal how much the society needs to pay for one non-case of PTSD. This study is therefore set to be the definitive trail internationally.

Second, a unique aspect of this clinical research study is that we will examine the underlying mechanisms of the treatment, drawing on work in basic neuroscience and cognitive theory. The intervention is hypothesized to modify the trauma memory, and thus to prevent the development of PTSD symptoms, before any major memory consolidation has taken place (i.e. sleep on night one[^31^](#_ENREF_31)) which would otherwise cement the traumatic memories in a maladaptive way. It would therefore be of great scientific value to see if the stipulated effect of the emotional processing theory, which TF-CBT draws upon, applies within this preventive context in a non-psychiatric sample. We will also investigate the role of different emotions and their consequences in treatment outcome. There is a lot of research on fear extinction but, as many other emotions are involved in PTSD as well as other mental disorders, the next step would also to investigate the role of disgust, shame etc. and see if these emotions follow the same path as fear extinction. Research about emotional memory consolidation and treatment mediators would give us highly valuable information both about the etiology of PTSD, and also information on how to treat PTSD in the most effective way with psychological interventions. If we know how our treatment works optimally, we can implement additional instruments and procedures that ensure that we activate the working mechanisms in this treatment. Critically, this study will also be able to demonstrate whether treatment success (or failure) is contingent on the hypothesized mechanisms. Therefore this study will be among the first to link the basic laboratory work on memory consolidation to an applied real world setting.

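### The cost term in the ICER and the net benefit is written as a change from baseline with no cost windows; it should be cost accumulated from randomisation, with pre-trauma cost as a covariate

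*Protocol*

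**What the plan says.** Protocol, Methods 2.3, writes out two formulas.

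- **ICER.** The numerator "is the difference in cost change (from pre- to follow-up) between the two treatment groups". The denominator "refers to the corresponding difference in clinical outcome (i.e. PTSD vs. no PTSD".
- **Net benefit.** For each patient the plan takes lambda times E and subtracts a cost term. There "E is the efficacy (i.e. PTSD status or gain on the EQ-5D", and the cost term "is the cost change from baseline to primary endpoint (6-months". The individual values go into a bootstrapped regression that compares the arms, and acceptability curves are drawn.

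Section 2.3 gives no window for the baseline cost or the follow-up cost, and does not say that cost is summed from randomisation.

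Three other places bear on this:

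- Methods 2.2, on the psychologist's cost: "The treatment costs (i.e. the cost of having a full time psychologist at the emergency department) will be included in the cost estimation".
- Methods 2.1 sets a societal perspective and takes data from linked registers.
- Scientific implications says that "the health economical analyses will reveal how much the society needs to pay for one non-case of PTSD".

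On timing, Methods 1.1 places baseline after the trauma and before allocation, TF-CBT within 72 hours of the accident, and the primary endpoint at 6 months after the trauma.

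**The concern.** Cost is a flow. Unlike a symptom score it has no value at a visit, so a pre-to-post change means nothing until two periods are named. The price of a prevented case needs the difference between arms in total resources used over a defined period.

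As written, the term can be computed in ways that do not agree. One of them leaves out what was spent between baseline and 6 months, which is where much of the sick leave and care avoided by preventing PTSD would fall. The ICER, the individual net benefits and the acceptability curves all use this term, so the answer to research question 2 depends on how it is read.

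**Working it through.** The protocol gives no cost, ICER or net-benefit figure, so there is nothing of its own to reproduce. All cost inputs below are assumptions. The control risk of 20% matches the share that the protocol's background section gives for PTSD after trauma; the other risks, unit costs, SDs and correlations are illustrative.

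**Reading A: cost level at 6 months minus cost level at baseline**

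Assume a PTSD risk of 20% vs 12% (difference 0.08), a case costing 10 units per month in months 2 to 6 (5 months), and a TF-CBT cost of c per patient. The expected baseline level is equal in the two arms by randomisation.

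- True incremental cost to 6 months: c - 0.08 x 10 x 5 = c - 4.0.
- Level change, TF-CBT cost left out: -0.08 x 10 = -0.8, whatever c is.
- Level change, TF-CBT cost added back as Methods 2.2 implies: c - 0.8.

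Even in the last case, 4.0 - 0.8 = 3.2 units of averted cost are lost. With c = 2 the truth is a saving of 2.0 and the rule reports a cost of 1.2. The sign is wrong for any c between 0.8 and 4.0.

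A second set of inputs: TF-CBT 6000 per patient, risk 20% vs 10%, a case costing 4000 per month for 6 months.

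- Truth: 6000 - 0.10 x 4000 x 6 = 3600, or 3600/0.10 = 36000 per case averted.
- Level change without TF-CBT cost: -0.10 x 4000 = -400, or -4000 per case.
- Level change with it added back: 6000 - 400 = 5600, or 56000 per case. The sign is right, but the price is too high by 20000.

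**Reading B: cumulative 6-month cost minus cost over a pre-trauma period**

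Expected pre-trauma cost is equal in the two arms, so the expected numerator is unchanged. A simulation with 176 per arm and the second set of inputs gave mean differences of 3594 (change) and 3583 (cumulative), against an expected 3600. The standard errors were 1756 and 1531, a ratio of 1.15.

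For precision, let k be the pre/post SD ratio and rho the pre/post correlation, and scale the post-period variance to 1.

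- Change score: 1 + k^2 - 2 rho k.
- Unadjusted cumulative cost: 1.
- Cumulative cost with pre-period cost as covariate (large sample): 1 - rho^2.
- Change score relative to covariate adjustment: (1 + k^2 - 2 rho k)/(1 - rho^2) = 1 + (k - rho)^2/(1 - rho^2), which is never below 1.

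| k | rho | Change vs covariate-adjusted | Change vs unadjusted |
|---|---|---|---|
| 1 | 0.1 | 1.82 | 1.80 |
| 1 | 0.3 | 1.54 | 1.40 |
| 1 | 0.5 | 1.33 | 1.00 |
| 0.5 | 0.1 | 1.16 | 1.15 |
| 0.5 | 0.3 | 1.04 | 0.95 |
| 0.5 | 0.5 | 1.00 | 0.75 |

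Entries are variance ratios for the cost difference. Against unadjusted cumulative cost, subtraction is worse only when rho < k/2. The largest ratio, 1.82, means an interval about 35% wider (square root 1.35) than with covariate adjustment.

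**The case against.** The case for leaving the text alone has four parts.

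1. **Reading A is strained.** Methods 2.2 includes the treatment cost, and register data on sick leave, admissions and drugs are naturally summed over time. A reader might infer that the formula drops the cost of TF-CBT and so makes a costly treatment look cost-saving. The protocol does not support that, because the inference has to set Methods 2.2 aside. What stands is narrower: 2.3 does not say where the treatment cost enters, and adding it back does not recover the other costs between the two points.
2. **Under Reading B the estimand is intact.** A reader might infer that the result cannot be the price of a prevented case. That goes too far. With 1:1 randomisation the expected pre-trauma costs cancel, and individual net benefits serve only to estimate the difference between arms. This part stands in full, and what remains under Reading B is precision.
3. **Subtraction need not add noise.** Against unadjusted cumulative cost it helps when rho > k/2, so a general claim that it widens the interval would be false. It still never beats covariate adjustment asymptotically.
4. **The phrase may loosely mean cost accrued over the interval, and windows can be left to an analysis plan.** Accrued cost is a possible meaning, although the ICER's pre-to-follow-up wording points to a difference between two periods. Windows and covariates may well be set in an analysis plan that is not shown. The formula itself, however, is fixed in the protocol, and it is a change score.

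**Conclusion.** The point holds as a fault in how the cost term is fixed; it does not show that the economic result must be wrong. Both formulas specify a change from baseline without cost windows, while the stated aim calls for accumulated cost.

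- As a difference of levels, the term loses the cost between the two points even with TF-CBT included, and the sign can be wrong (under the first set of assumed inputs, for c between 0.8 and 4.0).
- As a difference of periods, it is unbiased, with a variance about 1.0 to 1.8 times that of a baseline-adjusted analysis for k of 0.5 to 1 and rho of 0.1 to 0.5.
- As accrued cost, it is right and needs only clearer wording.

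The sizes rest on assumed inputs. The variance ratio is a large-sample result for the cost component and does not describe the whole net benefit. The matter is confined to research question 2; the primary CAPS analysis is unaffected. It should be corrected before costs are analysed.

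**What to change.** In Methods 2.3:

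- Define C as total societal cost from randomisation to the analysis time point, including the cost of TF-CBT, in line with Methods 2.2.
- Use C1 - C2 as the ICER numerator and (lambda x E) - C as the individual net benefit. Keep both planned effect measures, PTSD status and EQ-5D.
- Name a fixed pre-trauma window, and enter the cost over that window as a covariate in the net-benefit regression already planned instead of subtracting it.

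The cost is a change of wording and one covariate. The one extra demand is that the pre-trauma window must be set and its costs extracted from the linked registers. Methods 2.1 speaks only of following patients in those registers and does not mention a look-back period. A period-based change score would need the same pre-trauma data, so on that reading nothing is added. If accrued cost was intended all along, the new wording makes that plain and the covariate can still add precision.
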